## Abstract

Sleep problems are widespread among children and can have a negative impact on their development, everyday functioning and pose an additional burden on the parents. While there are numerous apps designed to improve children’s sleep and help them fall asleep, little data are available regarding the feasibility, acceptability and efficacy. The purpose of this study is to conduct an initial analysis of the feasibility and acceptability of the Aumio app and an email psychoeducational module as well as preliminary efficacy on child’s sleep quality and the associated factors well-being and parental stress. This research project is designed as a single-group pre-post design for a sample of 456 guardian-child dyads, with children aged 6–12 years. Participants will be recruited through the Aumio app as well as through advertisements in pediatric clinics and online. During the 12-week intervention, participants will be provided with the Aumio app and the parent-centred email psychoeducation module. At the beginning of the intervention and before the first app use (T0), six weeks after the first app use (T1), and immediately following the conclusion of the 12-week intervention (T2), the feasibility, acceptability and preliminary efficacy on children’s sleep and health-related quality of life as well as parental stress will be examined. The study will examine the association between the intensity of the Aumio app use and the endpoints to improve feasibility and acceptability by synthesizing recommendations for use. This pilot study can provide important insights into an app targeting child’s sleep problems in naturalistic, uncontrolled settings. Through this study, the existing research gap regarding app-based interventions for improving infant sleep will be addressed. Results will stimulate further development and research in the area of evidence-based mobile health interventions for children and their parents.

## Introduction

Sleep problems are widespread among children in Germany, affecting more than 20% of children of preschool and primary school age [1]. The most common sleep problems in this age group are difficulties with falling or staying asleep, which may persist and remain for extended periods [2]. Simultaneously, sleep plays a crucial role in child development and is closely linked to physical, cognitive, behavioural, and social-emotional functions that affect children’s learning, behaviour, and overall well-being [3]. Furthermore, sleep is crucial for the development of complex executive, verbal and non-verbal cognitive functions [3]. Consequently, childhood sleep problems are associated with a variety of secondary impairments [4]. According to a recent review [3], a variety of detrimental outcomes are associated with insufficient sleep duration in children: insufficient sleep duration increases the risk of overweight or obesity and related health conditions in children. Moreover, insufficient sleep may be a risk factor for later development of ADHD and may lead to an increased occurrence of externalising behaviours such as hyperactivity, impulsivity, irritability, and conduct problems [5]. Other effects include daytime sleepiness and impaired daytime functioning, short attention span, and negative behavioural responses and interactions with peers [3]. Additionally, insufficient sleep, inadequate sleep (i.e., a shorter sleep duration than required to maintain daytime wakefulness), poor sleep quality, and especially sleepiness during the day are associated with problems in children’s learning, memory, and academic performance [6].

Given that sleep problems in toddlers and school-aged children can also negatively affect parents’ sleep, health, and daytime functioning [7], addressing parental burden in this context is particularly relevant. A meta-analysis by Varma, Conduit, Junge, Lee, and Jackson [8] found associations between child sleep problems and poorer sleep quality on side of the parents, more severe insomnia symptoms, and increased arousal before parents go to sleep. In addition, poor child sleep has been negatively associated with the parents’ partnership quality and between parent and child relations [9]. Therefore, addressing parental burden within interventions for child’s sleeping problems is a promising approach, not only for the parents themselves, but also with respect to possible influences on children’s therapy processes and outcomes [10].

A meta-analysis conducted by Zhu, Xiao, and Tu [11] covering 15 studies demonstrated that technology-based interventions can contribute to the improvement of children’s sleep by increasing the total sleep time, sleep efficiency as well as decreasing the sleep onset latency and time span awake after sleep onset. Although the effect sizes were generally small to moderate, the studies demonstrated good overall quality. However, there was high heterogeneity in the data and the types of technology used. Additionally, the majority of technology-based interventions targeted children’s caregivers by providing sleep behavior management strategies and parental stress was not addressed. While the six uncontrolled pre-post studies demonstrated significant mean effect size in all outcome indicators, the eight randomized controlled trials only showed effects in wake after sleep onset. However, the trials conducted so far included 5 different intervention types. Up to now, there is limited research on audio-based mobile applications for improving children’s sleep quality [12].

To date, the Aumio app has been evaluated in a few unpublished master’s theses. However, this marks the first scientific study to assess the Aumio app using a large sample size, following a preregistered study protocol, with the intention of disseminating the findings. We aim to investigate the feasibility and acceptability of the Aumio app and the email psychoeducational module. As secondary user-centred outcomes, preliminary efficacy on child’s sleep quality and associated factors will be investigated. This current trial aims to fill a gap in research by being the first to investigate the feasibility and application of a German-language audio based app for improving children’s sleep quality with a large sample in a naturalistic setting. Additionally, the study examines preliminary’ efficacy of the Aumio app on child’s sleep quality, health related quality of life and parental stress as well as the concurrent application of a parent-centred email psychoeducation module.

### Objectives

The aim of this pilot study is to test the feasibility, acceptability and preliminary efficacy of the Aumio app and the parent-centred email psychoeducation module. We aimed (1) to examine the feasibility and acceptability of the of the Aumio app and the parent-centred email psychoeducation module. We therefore aimed to conduct qualitative and quantitative data to gain comprehensive insights. In addition, we also aimed (2) to collect information for improvements of the Aumio app and the parent-centred email psychoeducation module from a user’s perspective. We furthermore aimed (3) to examine the preliminary efficacy of the Aumio app and the parent-centred email psychoeducation module. As secondary user-centred outcomes, we aimed to examine whether its use improves children’s sleep, covering a broad range of facets to adequately capture the multidimensional nature of sleep. Furthermore, preliminary efficacy on child’s health-related quality of life and effects on parental stress will be tested as secondary user-centred outcomes. In order to further improve the feasibility and to synthesize recommendations for use, it will be investigated (4) at which intensity of usage the Aumio app significantly affects the feasibility and satisfaction as well as the secondary user-centred outcomes. The intensity of usage will be analysed continuously as well as divided into 4 levels (12, 18, 24, and 30 uses during the study period) and included in the analyses.

The primary, feasibility hypothesis refers to the user’s subjective perspective on the Aumio app and the parent-centred email psychoeducation module, with the assessment time points 6 weeks after the start of the app use, at the midpoint of the 12-week parent-centred email psychoeducation module and again another 6 weeks after. We hypothesize that the Aumio app and the parent-centred email psychoeducation module is feasible. We also hypothesize Aumio app and the parent-centred email psychoeducation module is accepted among the users. We further hypothesize that the present study design is feasible to conduct a large scale trial on the effectiveness.

The secondary, user-centred hypothesis refer to comparisons of endpoint scores pre app use, at the same time points as the feasibility survey. We hypothesize that 6 weeks and 12 weeks after the start of the app use, children’s sleep quality will be significantly increased (secondary, child-centred endpoint) and health-related quality of life will be significantly higher (secondary, child-centred endpoint). Furthermore, we hypothesize that parenting stress will be significantly reduced 12 weeks after the start of the use of the email psychoeducational program (secondary, parent-centred endpoint). Exploratory analyses will also be conducted to determine to what extent usage behavior influences the effects on primary and secondary outcomes.

## Methods

### Ethics approval and consent to participate

Ethical approval and modification approval were granted by the Ethics Committee of the Department of Education and Psychology of Freie Universität Berlin on February 07, 2023, under reference number 047.2022.

### Trial design and study setting and participant timeline

The present research project is designed as a one-group pre-post pilot study. As this trial is the first larger scale pilot trial on the feasibility and acceptability as well as the first trial on the preliminary efficacy of the app on sleep quality and the parent module, randomization, control groups, and blinding do not apply to the study design of this trial. The study is a single study conducted in the naturalistic setting of the app, meaning it was conducted exclusively in-app and within a German-speaking population. After consenting to participate in this study, the participants will be provided a 12-months free access to the Aumio app and receive the parent-centred email psychoeducation module at weekly intervals.

Once participants agree to the conditions of participation and meet the inclusion criteria, guardians are directed to the first assessment (T0). At T0, at the beginning of the intervention and before the first app use, data on sociodemographic characteristics and relevant covariates and the outcomes will be collected. After completing the first survey T0, participants are provided with free access to the Aumio app for one year and receive the parent-centred email psychoeducation module once a week. The intervention duration is set at twelve weeks. Six weeks after the intervention start and the first app use, the second measurement point (T1) takes place, where primary and secondary outcomes are assessed. Immediately following the conclusion of the 12-week intervention, the third measurement point (T2) is conducted, comparable to the T1 assessment (Fig 1).

**Fig 1 pone.0322302.g001:**
[figure not shown]
SPIRIT schedule of enrolment. CSHQ = Children’s Sleep Habits Questionnaire. SI-KJ = Sleep inventory for children (Schlafinventar für Kinder und Jugendliche), EBI = Parenting Stress Index (Eltern-Belastungs-Inventar).

### Eligibility criteria

In line with the naturalistic setting of the study, the age range was set according to the target population of the Aumio app. Participants are eligible if the children are between 6 and 12 years old. The following exclusion criteria will be collected, assessed, and applied at T0: (1) insufficient German reading and understanding language proficiency of the child or guardian, (2) impaired hearing ability of the child, (3) diagnosed intelligence impairment or other severe developmental disability of the child, and (4) diagnosed obstructive sleep apnea of the child.

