### Intervention description

The intervention consists of two components: the Aumio app and the parent-centred email psychoeducation module. Both are made available to participants. Aumio is a smartphone application designed to provide easily accessible health interventions for children and to promote healthy sleep and strengthen children’s mental health. It focuses on children’s sleep, relaxation, concentration and emotions. In the sleep module, Aumio offers a variety of audio stories, fantasy journeys and sounds for falling asleep to make going to bed in the evening as relaxing as possible for children. In addition, psychoeducation and the playful learning of relaxation techniques by means of meditations and dream journeys are integrated into the Aumio app. The meditation techniques are taught in a child-friendly way and made easily accessible for children. The exercises and stories are based on cognitive-behavioral techniques such as autogenic training or progressive muscle relaxation. The meditations and dream journeys for falling asleep have a duration between 5 and 20 minutes. In the intervention, families are advised to use the Aumio app at least twice a week in the evening, before bedtime. However, participants are encouraged to integrate the Aumio app into their daily routine in a manner that is suitable for them.

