The acceptability of the Aumio app and the parent-centred email psychoeducation module will be assessed both quantitatively and qualitatively by examining the user’s satisfaction. The questions are derived from a study by Hiscock et al. [13], which examined the effects of a digital sleep intervention on child sleep and psychosocial outcomes of children and their caregivers. Satisfaction is assessed on 5-point Likert scale (1 = totally disagree/very unsatisfied, 5 = totally agree/very satisfied) generally and by specific factors, including satisfaction with the use of the product (“The app was easy to use”; “The e-mail course was understandable.”), the information provided (“The amount of information in the app was just right.”; “I was satisfied with the content provided by the app.”; “The amount of information in the e-mail course was just right.”; “I was pleased with the strategies the email course provided for my child’s sleep problem”; “I would have preferred to have a personal contact instead of the e-mail course to explain the strategies and their application.”), the feeling of safety (“I felt safe using the app.”; I felt safe participating in the email course.”), the subjective perception of improvement in the child’s sleep (“Using the app has helped my child to fall asleep.”; “Taking part in the e-mail course has helped my child to fall asleep better.”), and the intention to continue using the product in the future (“I would like to continue using the e-mail course in the future.; “I would like to use the app in the future.”). Likelyhood of recommendation to other parents (“How likely is it that you will recommend the Aumio app to other parents you know?”, “How likely is it that you will recommend the e-mail course to other parents you know?”) will be assessed using a 10-point Likert scale (1 = unlikely, 10 = highly likely). Quantitative data will be further supplemented by qualitative data on helpful content (“What has helped you and your child the most with the Aumio app?”, “What did you and your child find particularly helpful about the email course?”), ideas for improvement (“What would you change to improve the Aumio app?”, “What would you change to improve the email course?”), as well as moments when users experienced difficulty using the app (“When did you find it difficult to use the Aumio app?”). Additionally, we will assess changes in sleep duration (“Has your child’s sleep duration changed with the use of Aumio and the e-mail course?”) and whether parents sought advice from their local paediatrician regarding sleep problems (“While using the Aumio app and email course, did you contact your local paediatrician for more information on how to help your child sleep?”).

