### Recruitment and treatment allocation

Participants are recruited and allocated consecutively. Study participants are mainly recruited through the Aumio app. After downloading the app in the app store, five percent of new users are offered the chance to enrol in the study before they start using the app for the first time. Recruitment will be augmented by advertisements in pediatric clinics and online, where a link to the website in the survey platform for informed consent is provided. If parents are interested in the study, they will be redirected to a dedicated page within the app. On this page, both children and guardians receive information about the opportunity to participate in the study. Participants are informed about the purpose and process of the survey, as well as possible advantages and disadvantages of participating. They will be informed that participation in the study is completely voluntary and that participation can be terminated at any time without giving reasons. Furthermore, participants will be informed about their rights regarding data storage, data protection and data deletion. Informed consent will be obtained from both guardians and children in child-friendly language.

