### Methods for additional analyses

Additional analyses will be conducted to examine whether effects differ between groups with different sociodemographic characteristics, e.g., household size, parental education, parental income, relationship conflict between parents, parental separation, co-sleeping and media use. We will therefore evaluate the effects of including sociodemographic characteristics as covariates in an analysis of covariance (ANCOVA).

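### Entry is open whatever the child's sleep, yet one acceptability item assumes a sleep problem, two more imply one, and no described analysis reports results by sleep at T0

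*Protocol article*

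**What the plan says.** All references are to the protocol article.

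- *Eligibility criteria*: "Participants are eligible if the children are between 6 and 12 years old". Of the four exclusions only one concerns sleep: "diagnosed obstructive sleep apnea of the child".
- *Recruitment and treatment allocation*: the main route is the app itself, where "five percent of new users are offered the chance to enrol in the study before they start using the app for the first time". Advertisements in paediatric clinics and online add to this. No sleep screen is described.
- *Abstract*: "This pilot study can provide important insights into an app targeting child’s sleep problems in naturalistic, uncontrolled settings". The *Discussion* places the study's importance in the same field and says that the results will inform a later randomised trial.
- *Intervention description*: the app's purpose is broader, "to promote healthy sleep and strengthen children’s mental health", and its content also covers relaxation, concentration and emotions.
- *Primary, feasibility outcome*: satisfaction is rated from 1 to 5. One item begins "I was pleased with the strategies the email course provided for my" and ends by naming the child's sleep problem. Two others ask whether the app, or the email course, helped the child to fall asleep.
- *Trial design and study setting and participant timeline*, with *Secondary, user-centred outcomes*: outcomes are collected at T0, and they include the CSHQ and the Sleep Inventory for Children (SI-KJ).
- *Statistical methods for primary and secondary outcomes*: feasibility, acceptability and app use are summarised descriptively; change is analysed by repeated measures ANOVA.
- *Methods for additional analyses*: the aim is to "examine whether effects differ between groups with different sociodemographic characteristics". The examples are household, education, income, relationship, co-sleeping and media variables.

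**The concern.** Families can join for reasons other than poor sleep, so the sample will mix children with and without a sleep problem in unknown proportion. Two things follow.

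First, a guardian whose child sleeps well has no meaningful mark to give on strategies for that child's sleep problem. A low or middle mark may mean dissatisfaction, or only that the question does not apply. These items belong to the primary outcome.

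Second, if acceptability, use and dropout are reported only for the whole sample, a poor result could mean that the intervention did not suit families with a sleep problem, or that many families had nothing to improve. A good result could come mainly from good sleepers. The randomised trial that this pilot is meant to prepare needs to know which.

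**Working it through.** **1. The plan's own figures.** *Sample size* gives d = 0.21, alpha 0.05, power 0.90, n = 196, and 456 after 57% dropout. For a paired t-test, the one-sided normal approximation gives ((1.645 + 1.282)/0.21)² ≈ 194.3, so 195. The exact noncentral t calculation gives 196 (power 0.9006). The article does not state sidedness; a two-sided test would need 241. Dropout: 196/(1 − 0.57) = 455.8, so 456. Both figures reproduce. Neither contains a term for the share of children with a sleep problem, so this point is not a sample-size error.

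**2. The items.** The article quotes 13 specific five-point items. One names a sleep problem, two imply difficulty falling asleep, and 13 − 1 − 2 = 10 (ease of use, amount of information, safety, future use and the like) can be answered by any guardian.

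**3. Data held against analyses described.**

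| Result | Described analysis | T0 sleep as subgroup or covariate? |
|---|---|---|
| Acceptability | Descriptive, plus themes from open answers | Not named |
| App use, dropout | Descriptive | Not named |
| Change in CSHQ | Repeated measures ANOVA | No; the T0 score enters only as the pre-measurement |
| Covariate analyses | ANCOVA, example list | Not named; co-sleeping is the nearest entry |

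The T0 scores needed for a breakdown are collected in every case.

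**4. What a breakdown could show.** The share with a sleep problem is not given, so it is an assumption here. The *Introduction* offers only a background rate, "affecting more than 20% of children of preschool and primary school age", and users of a sleep app may well exceed it. Dropout is taken as equal across groups. Half-width of the 95% interval for a 50% rate: 1.96 × √(0.25/n), with n the completers. Power is for a one-sided paired t-test at d = 0.21.

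| Assumed share | Enrolled, of 456 | Completers, of 196 | Half-width (points) | Power |
|---|---|---|---|---|
| 20% | 91 | 39 | 15.7 | 0.36 |
| 50% | 228 | 98 | 9.9 | 0.66 |
| 75% | 342 | 147 | 8.1 | 0.81 |
| All children | 456 | 196 | 7.0 | 0.90 |

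A subgroup of these sizes supports a rough description of acceptability. At the lower shares it is too small for a useful test of change.

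**The case against.** The case against is strong on several counts.

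- **Broad entry is deliberate and coherent.** The age range follows the app's target population, the app is described as promoting healthy sleep, and d = 0.21 comes from universal prevention programmes. Acceptability among actual users is a sensible question. This stands, and eligibility should not change.
- **The data exist.** A reader might infer that the trial cannot answer for children with sleep problems. The documents do not support that: both sleep questionnaires are collected at T0, so the breakdown is a re-tabulation.
- **The list of additional analyses is open.** It is introduced by way of example, and an analysis plan that is not shown may name baseline sleep. This stands, so the missing breakdown is a recommendation and not a proven omission.
- **The item problem is narrow.** Ten of 13 items are unaffected, no composite score is defined, and use and dropout do not depend on item wording. The article gives the scale anchors but does not say whether items can be skipped. If the full questionnaire already has a not-applicable option, that part of the point falls away.
- **Dilution of the effect size.** A reader might divide 0.21 by a prevalence to obtain the effect required in affected children. The documents give no basis for this: 0.21 is already an average from universal programmes, and the division assumes no change at all in every other child.

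What remains is the item as described. A split by T0 sleep would show which group a low mark came from, but not whether a good sleeper's guardian was dissatisfied or had nothing to rate. That has to be settled when the answer is collected.

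**Conclusion.** The point holds as a modest, inexpensive improvement. Entry is unselected on sleep while the study is presented as informing on an app for sleep problems. One acceptability item has no valid answer on its scale for some eligible families, and two more are doubtful for them. No described analysis uses T0 sleep to break down acceptability, use, dropout or CSHQ change. As described, the trial will not say how the app suits children with sleep problems, although its data would allow it.

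The size depends on an unknown share. At an assumed 20% to 75%, between 39 and 147 of 196 completers would speak to the question, with half-widths of about 16 down to 8 points for a 50% rate. The conclusion rests on the article's description of the questionnaire and analyses being complete on these points. It implies no fault in the eligibility rule or in the figures 196 and 456.

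**What to change.** 1. Leave eligibility unchanged.
2. Add to the three items an option stating that the question does not apply because the child has no sleep problem. Tie it to the start of the study, so that a guardian whose child has since improved does not choose it. Leave these answers out of the items' denominators and report their number.
3. Report acceptability, app use and dropout by T0 sleep, either against the continuous score or by a cut-off fixed before the data are seen. State a rule for children older than the norm samples given under *Secondary, user-centred outcomes*: over 10 years for the CSHQ, over 11 for the SI-KJ.
4. If CSHQ change is shown by baseline sleep, keep it descriptive and classify by the T0 SI-KJ, because grouping on the CSHQ's own baseline would add regression to the mean. Some will remain and should be stated.

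Cost: one answer option on three items, a classification rule and a few tables, with no new assessment. The price is smaller groups and wider intervals, at worst about 16 points in the 20% scenario, and a cut-off that the norms do not support for the oldest children.

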
#### Secondary, user-centred outcomes.

For the assessment of child’s sleep quality, we used the Children’s Sleep Habits Questionnaire (CSHQ, 14]). The CSHQ is a retrospective screening instrument designed to examine children’s sleep [14]. It consists of 48 items, with 33 items distributed among various subscales, including bedtime problems, difficulties in falling asleep, sleep duration, anxiety, nighttime awakenings, parasomnias, breathing disorders, and daytime sleepiness. These subscales are utilized to calculate an overall score, providing a comprehensive evaluation of children’s sleep. Additionally, bedtime, the child’s average amount of sleep per day, duration of nocturnal wakefulness, and morning awakening time are recorded [14]. The German adaptation of Schlarb [15] is used, which was validated and normed by Schlarb, Schwerdtle, and Hautzinger [16] among a German norm sample consisting of 298 parents of 4–10-year-old children and 45 parents of children with sleep disorders.

To cover more aspects of sleep quality, we amended the CSHQ [14–16] by the Sleep inventory for children (Schlafinventar für Kinder und Jugendliche, SI-KJ; [17]). The retrospective, 33-item screening instrument supplements the survey by assessing sleep hygiene and sleep environment characteristics as well as physical factors contributing to sleep problems [17]. The questionnaire contains the main scale sleep and daily behaviour and the subscales sleep onset and sleep through problems, vegetative symptoms, daytime sensitivity, and nocturnal events. Data on various characteristics of sleep hygiene and sleep environment as well as physical factors, e.g., health problems such as allergies or chronic diseases are assessed. The instrument has been validated and normed on a German norm sample of 5–11-year-old children and parents [17].

We used the German version of the KiddyKINDL and KidKINDL, retrospective 24-item instruments to assess the health-related quality of life [18,19]. The KiddyKINDL is administered to guardians of 6-year-old children, and the KidKINDL is administered to guardians of 7–12-year-old children. Contents of the questionnaires are the subscales physical well-being, psychological well-being, self-esteem, family, friends, and functioning in daily life (school or preschool/kindergarten), with 4 items each [18,19]. Both versions are publicly available, have been psychometrically tested [20] and German normative scores are available [21].

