A limitation of the study design is the way in which the secondary user-centred objectives are collected. These are exclusively collected retrospectively in the third-party report by one parent. In particular, children’s sleep quality is not recorded in self-report. This approach may overlook potential cases of sleep problems in children, as highlighted by Paavonen et al. [36], who suggest that one-third of such cases may go undetected if only parents are surveyed. Therefore, it would have been beneficial to include both children’s and guardians’ perspectives in assessing children’s sleep. Due to the target group of children aged 6–12 years, sufficient reading skills are not to be expected in a comparatively large number of cases until the age of 7 or 8 years. Another limitation is the use of subjective, parent reported methods for assessing children’s sleep, without incorporating objective measures. Subjective methods for data collection depend on self-reported information and may be influenced by biases or inaccuracies [37]. Objective methods that directly measure sleep and recovery function and thus provide indirect information about sleep quality were not used [37]. In particular, discrepancies in the recording of total sleep time and wake after sleep onset have been reported in several studies [38]. This inconsistency must be considered when interpreting the data and highlight the need for a comprehensive approach that combines subjective and objective measures to obtain a more accurate understanding of sleep. Future studies should consider incorporating children’s self-report and guardians report as well as objective measures of sleep to provide a more comprehensive assessment of sleep quality.

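### Exclusion criterion 1 names the child's German reading proficiency, although the protocol says many children lack it until age 7 or 8, plans for 6-year-olds, and describes no outcome that needs a reading child

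*Protocol article*

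**What the plan says.** Under Eligibility criteria, the protocol article explains that "the age range was set according to the target population of the Aumio app" and states: "Participants are eligible if the children are between 6 and 12 years old". The same paragraph continues "The following exclusion criteria will be collected, assessed, and applied at T0", and the first criterion on that list is "1) insufficient German reading and understanding language proficiency of the child or guardian". The criterion names reading as well as understanding, and the child as well as the guardian. It sets no separate standard for the child and none that varies with age.

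Two other sections bear on this:

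- Secondary, user-centred outcomes: "The KiddyKINDL is administered to guardians of 6-year-old children". Guardians of children aged 7 to 12 complete the KidKINDL instead.
- Discussion, on limitations: the secondary outcomes are "exclusively collected retrospectively in the third-party report by one parent". In explaining why children's own view of their sleep was not collected, the article says that "sufficient reading skills are not to be expected in a comparatively large number of cases until the age of 7 or 8 years".

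**The concern.** The measurement plan treats children who cannot yet read as participants. The Discussion counts them in the target group, and the health-related quality of life measure has a version for the age at which they are most common. The eligibility paragraph, read as written, excludes them.

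This matters more here than in many trials because the primary outcome is feasibility, which includes how recruitment works, and the study is meant to inform a later randomised trial. A criterion that depends on reading also selects within the youngest ages: early readers stay and the others go. Satisfaction and usage among 6- and 7-year-olds would then describe a selected group. If guardians instead differ in how literally they take the word, the age mix depends partly on how the criterion was understood, and the recruitment figures carry that noise.

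**Working it through.** **Step 1: does any outcome need a child who can read?** Each described use was checked.

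| Element | Section of the protocol article | Who reads or answers |
|---|---|---|
| User numbers, dropout, usage, recruitment | Primary, feasibility outcome | No questionnaire for the child |
| Satisfaction and recommendation items | Primary, feasibility outcome | Parent (items refer to the respondent's child and to other parents) |
| Weekly quiz | Intervention description; Primary, feasibility outcome | Tests the content of the parent email module |
| CSHQ, SI-KJ, KINDL, EBI | Secondary, user-centred outcomes; Discussion | One parent |
| Evening content of the app | Intervention description | Child listens (stories, fantasy journeys, sounds) |
| Study information and assent | Who will take informed consent? | Child receives written, child-friendly text |
| Info sheet attached to the weekly email | Intervention description | Child-friendly text |

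The last two rows are the only written material for the child, and neither is an outcome.

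**Step 2: can the three statements operate together?** Eligibility opens at 6 years, and the KiddyKINDL is planned for that age. The Discussion says that sufficient reading is often absent until 7 or 8. Criterion 1 excludes for insufficient reading. A 6-year-old who understands German well but does not yet read is admitted by the first, expected by the second and excluded by the third.

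**Step 3: how large could the loss be?** The article gives neither an age distribution nor a share of non-readers, so both are assumptions:

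- Ages spread evenly over the seven years 6 to 12. One year is then 1/7 = 14.3% of otherwise eligible children, and two years are 2/7 = 28.6%.
- Share of non-readers in the affected years, u: from 0.30 to 1.00.

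Share lost = (share of sample in the affected years) × u. Number of otherwise eligible children to screen for 456 enrolled = 456 / (1 − share lost), rounded up.

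| Affected ages | u | Share lost | To screen for 456 |
|---|---|---|---|
| 6 | 0.30 | 0.143 × 0.30 = 4.3% | 477 |
| 6 | 1.00 | 14.3% | 532 |
| 6 and 7 | 0.30 | 0.286 × 0.30 = 8.6% | 499 |
| 6 and 7 | 1.00 | 28.6% | 639 |

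**Step 4: is the sample size touched?** The planned 456 reproduces from the article's own inputs. A one-sided paired t-test with d = 0.21, alpha 0.05 and power 0.90 gives 196, and 196 / (1 − 0.57) = 455.8, rounded up to 456. Nothing in that calculation depends on age or reading. The criterion changes who fills the 456 places, not how many are needed.

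**The case against.** The best defence is that the phrase was meant as command of German, not literacy. The study is set in a German-speaking population, the criterion speaks of language proficiency, and insufficiency can be judged against what the study asks of each person. Since the outcomes ask no reading of the child, a German-speaking first-grader would not be insufficient. The KiddyKINDL and the Discussion both point to that intention. This is plausible and may well be what the authors meant. It does not remove the problem: the text names reading, applies it to the child and is used at T0. Enrolment runs through the app and a survey platform, and no step is described at which staff would explain the criterion to the guardian.

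A second defence is that the T0 screening question is not printed, so no exclusion can be shown to occur. That stands as a limit on the conclusion. The criterion itself is printed, however, and it conflicts with other parts of the same article.

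A third is that children receive written information and an info sheet, which gives reading some purpose. That is fair, but a guardian can read both aloud.

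A reader might infer more than the article supports:

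- **That the youngest age band is removed and the KiddyKINDL group left nearly empty.** Only non-readers are affected, and the Discussion speaks of a comparatively large number of cases, not of most children. Total loss of an age year is only the upper end of the assumed range.
- **That about 65 or 130 of the 456 are excluded.** Those are 456 × 1/7 and 456 × 2/7, the size of whole age bands under even ages, not counts of exclusions.
- **That children's limited reading is the stated reason for parent report of every outcome.** The Discussion ties it to the child's own account of sleep. Parenting stress is the parent's own outcome in any case.

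**Conclusion.** The point holds as an inconsistency in the eligibility criteria. As written, criterion 1 would exclude children whom the outcome plan and the Discussion treat as participants, and no outcome described needs the requirement. The children at risk are the non-readers, mainly aged 6 and 7. Whether any are actually lost depends on how the T0 question is worded and answered, which the article does not show.

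If the criterion is applied literally, the loss is about 4–14% of otherwise eligible children (6-year-olds only) or 9–29% (6- and 7-year-olds). These figures rest wholly on the assumed even age distribution and the assumed 30–100% share of non-readers. If it is applied loosely by some guardians and literally by others, the loss is smaller but irregular. In both cases the feasibility, acceptability and recruitment results may not describe the stated 6–12 group.

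**What to change.** Reconcile the eligibility paragraph with the outcome section and the Discussion by splitting criterion 1 into two exclusions: insufficient German reading and comprehension of the guardian, and insufficient understanding of spoken German of the child. Align the T0 screening item with this wording. State that the guardian may read the child's written information and assent text aloud.

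The cost is a one-sentence amendment and one screening item, notified to the ethics committee. No procedure, instrument or sample size changes. If screening has already begun, report the number excluded under criterion 1 by the child's age, so that readers can see how the criterion worked.
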